### Data management

Clinical coordinators enter raw data from patient records into Case Report Form (CRF) in a timely and complete manner. Consistency of records in CRFs with original information regularly checked by inspectors. If the data analysts have questions about the data, the principal investigator will review the data in CRFs. All patients’ personal data and medical information will be kept confidential, and all participants will be assigned unique identifiers.

### The interim analysis

An interim analysis is performed on the primary endpoint when 50% of patients have been randomized and have completed the 12-month follow-up. The interim analysis is performed by an independent statistician, blinded for the treatment allocation. The statistician will report to the principal investigator, who makes the final decision to terminate the trial.

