### Randomization

Eligible patients will be randomized 1:1 into shunting the left (L Group) or right (R Group) branch of the portal vein. The randomization will be stratified by center, Child-Pugh class (Child-Pugh Class A=5–6 points or Child-Pugh Class B=7–9 points), and the serial ammonia level (lower level ≤ 50 µmol/L or higher level >50 µmol/L) before TIPS. The list will be balanced by different-sized blocks and randomly alternated. The treatment assignment of each eligible patients was generated by the web-based system and was contained in opaque envelopes. This randomization procedure was performed by the coordinator, who was isolated from data collection and analysis. The data coordination center of Zhongshan Hospital will prepare the randomization. Patients and clinicians will not be blinded to the shunting branch of the portal vein in TIPS, so the investigators who perform data evaluation and analysis will not participate in the randomization and treatment.

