### Sample size calculation

There is currently no multi-center RCT study on comparing the rate of HE between HBV-related cirrhosis patients with shunting left/right portal vein branches. The sample size was determined on the basis of three single-center study [11–13]: the rate of HE in the patients with left branch shunt was 19.4% (2 years after TIPS), 15.4% (2 years after TIPS) and 22.6% (1 year after TIPS), while the rate of HE in the patients with right branch shunt was and 43.8% (2 years after surgery), 37.5% (2 years after surgery), and 28.6% (1 year after surgery). We presume that the rate of HE after 2 years of TIPS shunting left and right branches will be 16.9% and 33.1%, respectively. Considering a power of 80% with a bilateral alpha risk of 5% and a dropout rate of 10%, we aimed to enroll 130 patients.

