### Statistical analysis

All data will be analyzed on the intention-to-treat population and are supplemented by per-protocol set analyses. The intention-to-treat population contains all patients who will undergo randomization (irrespective of whether they successfully receive TIPS), while per-protocol set analyses only include patients who successfully receive TIPS. Continuous variables will be summarized as mean ± standard deviation or the median values (ranges) and will be compared using the independent sample *t* test or one-way analysis of variance. Categorical variables will be expressed as frequencies and compared using the Chi-Square or Fisher’s exact tests. The missing data were performed with multiple imputation by using the MICE procedure. The time-to-event primary and secondary outcomes will be calculated by the Kaplan-Meier method and compared by the log-rank test (Mantel-Haenszel version). Data will be censored when any of the following events occur : liver transplantation, death, end of follow-up time. Estimates of treatment effect (with 95% CIs) were evaluated by using Cox regression models. Two-tailed *p* values <0.05 will be considered statistically significant. All statistical calculations will be performed using SPSS V.25.0 (Chicago, IL, USA).

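### The interim analysis can end the trial with no stated purpose or stopping criterion, while the full two-sided 5% is kept for the analysis; if efficacy stopping at p<0.05 is allowed, type I error is about 8.3%

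*Protocol article*

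**What the plan says.** All references are to the protocol article.

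- **The interim analysis.** There is one look: "An interim analysis is performed on the primary endpoint when 50% of patients have been randomized and have completed the 12-month follow-up". With 130 patients planned, that is 65 patients.
- **Who does it.** "The interim analysis is performed by an independent statistician, blinded for the treatment allocation".
- **Who decides.** "The statistician will report to the principal investigator, who makes the final decision to terminate the trial". The section names no efficacy, futility or harm criterion and does not say what the report contains.
- **Statistical analysis.** The only significance rule is "Two-tailed *p* values <0.05 will be considered statistically significant". Time-to-event outcomes, the primary one included, are compared by the log-rank test.
- **Sample size calculation.** "Considering a power of 80% with a bilateral alpha risk of 5% and a dropout rate of 10%, we aimed to enroll 130 patients". Nothing is reserved for an earlier look.
- **Study design and Outcome measures.** This is a superiority trial, and the primary endpoint is overt hepatic encephalopathy (HE) at 24 months.
- **Randomization.** Clinicians are not blinded to the branch shunted.
- **Study limitations.** An independent group of physicians does the follow-up and the diagnosis of HE blind.

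**The concern.** An analysis of the primary endpoint that can end a superiority trial is a second chance to declare a difference, unless its purpose is confined to futility or harm or a limit is set for it. The article does neither, and its own significance rule is an unadjusted 0.05. If that rule is applied at both looks, the trial does not have the 5% error on which it was sized.

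The second issue is who holds the result. The decision lies with the principal investigator, with no rule to apply. According to Recruitment and informed consent, the principal investigators explain the trial to eligible patients. According to Data management, the principal investigator reviews case report form data when analysts raise questions. One role therefore combines the interim report, the stopping decision, and contact with recruitment and data.

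Third, the interim trigger is 12 months of follow-up, whereas the endpoint is at 24 months. The quantity to be tested at the interim is not defined.

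**Working it through.** **Inputs.** From the article: one interim look at 65 of 130 patients with 12 months of follow-up; two-sided 0.05; 1:1 allocation; assumed 24-month HE rates of 16.9% (left) and 33.1% (right). Assumption, not in the article: the trial may stop for efficacy at the interim.

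**The plan's own figure.** A single two-sided test at 0.05 (critical value 1.960) has a type I error of 5%. The stated level is therefore right if there is only one opportunity to reject.

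**Two opportunities.** Under no difference, the interim and final test statistics Z1 and Z2 are approximately bivariate normal with correlation √t, where t is the information fraction at the interim. The overall error is 1 − P(|Z1| < c1 and |Z2| < c2).

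| t | p<0.05 at both looks | p<0.001, then p<0.05 | p<0.001, then p<0.049 |
|---|---|---|---|
| 0.25 | 0.0907 | 0.0506 | 0.0496 |
| 0.30 | 0.0893 | 0.0505 | 0.0495 |
| 0.40 | 0.0863 | 0.0504 | 0.0494 |
| 0.50 | 0.0831 | 0.0502 | 0.0492 |
| 0.60 | 0.0796 | 0.0501 | 0.0491 |

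The critical values are 1.960 for 0.05, 1.969 for 0.049 and 3.291 for 0.001.

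**Why a range of t.** The text does not fix t. A simulation assumed uniform accrual over 24 months, exponential event times and 25% HE at 24 months (the mean of 16.9% and 33.1%). It gave about 32.6 events in all. At the look there were:
- 8.7 events, counting the first 65 patients to month 12 only: t ≈ 0.27
- 12.5 events, counting the first 65 with all their follow-up: t ≈ 0.38
- 17.0 events, counting everyone enrolled by then: t ≈ 0.52

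**Limits that hold 5% at t = 0.5** (interim / final two-sided p):
- O'Brien-Fleming 0.0052 / 0.0480
- Lan-DeMets O'Brien-Fleming-type 0.0031 / 0.0490
- Pocock 0.0294 / 0.0294
- Haybittle-Peto 0.001 / 0.0498

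**Power cost of a final 0.049.** At 65 per arm and the article's own rates, power moves from 57.0% to 56.6%. That both figures fall short of the stated 80% is a separate matter of the sample size, and nothing here depends on it.

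**Enrolment at the look.** Trial status reports 55 patients from June 19, 2019 to May 27, 2021. That is 708 days, or 23.3 months, so 55/23.3 ≈ 2.36 per month. Assuming that pace continued, the 65th patient enters at 65/2.36 ≈ 27.5 months and reaches month 12 at about 39.5 months. By then 39.5 × 2.36 ≈ 93 of 130 are enrolled, and about 37 are still to be recruited.

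**The case against.** **This is an article, and limits are often left to the full protocol or analysis plan.** True, and a missing boundary alone would be no finding. But the article goes further than silence: it states an unadjusted 0.05 and gives the decision to the principal investigator without a criterion. A plan that reserved alpha or bound the decision would have to depart from one of these statements. It is fair to add that the 0.05 sentence is a general one and is not written as the interim rule.

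**A reader might infer that the trial, as written, has an 8.3% error.** The text does not support that without a condition. It speaks of termination without saying for what. A look for futility or harm only does not inflate type I error.

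**A reader might infer that unblinded arm-level results go to the principal investigator.** The article says only that the statistician reports, and that the statistician is blinded to allocation. Coded arms still allow a between-group test, so blinding does not remove the multiplicity. Nothing limits the report to a recommendation, but release of arm-level results is not stated.

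**A reader might infer that HE ascertainment is compromised.** The independent blinded assessors reduce that risk. They do not address recruitment or discretionary stopping.

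**A reader might infer that everyone is enrolled by the look, so that later recruitment is not at issue.** On the planned uniform 24-month accrual, the 65th patient would enter at month 12 and reach 12 months of follow-up at month 24, when accrual ends. The reported pace does not bear this out: about 37 patients would still be to come.

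**An early look is ordinary with a log-rank test.** This stands. The 12-month trigger is no error in itself; only the quantity tested needs to be named.

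**Conclusion.** The point holds in conditional form. The article plans an interim analysis of the primary endpoint that can end the trial, leaves its purpose and criterion undefined, and makes no allowance for it in the 5% used for sizing and testing. If stopping for efficacy at p<0.05 is possible, the overall type I error is about 8.3% at t = 0.5, and 8.0% to 9.1% for t from 0.6 to 0.25. This rests on the normal approximation and on the same 0.05 applying at both looks. If the look serves futility or harm only, the 5% is intact and what is missing is a statement to that effect.

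Separately, the open-ended report and the unguided decision expose the remaining recruitment and the decision to stop to knowledge of a trend. The article's blinding arrangements lessen the risk to HE diagnosis but do not cover these two.

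**What to change.** Before the look is taken, state:

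1. **Purpose and quantity.** Say whether the look is for efficacy, futility or harm, and what is tested: for example, the log-rank test on overt HE using all follow-up available at the data cut-off.
2. **If efficacy stopping is allowed.** Stop for efficacy only at two-sided p<0.001 (Haybittle-Peto) and test at two-sided 0.049 at the end. The overall error is then 0.0491 to 0.0496 for t from 0.6 to 0.25. An O'Brien-Fleming-type spending function at the observed event fraction is an alternative.
3. **If it is not allowed.** State that the trial will not stop for efficacy at the interim, and keep 0.05.
4. **Reporting.** The independent statistician gives the principal investigator only a continue/stop recommendation against the stated rule, with no arm-level results.

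The cost is a few sentences, a final level lower by 0.001 (about 0.3 percentage points of power in the calculation above), and less interim information for the principal investigator. No staff are added, because the independent statistician is already planned. A limit set after the look cannot be called prespecified. At the reported pace, the look would have fallen around October 2022, before the article appeared in May 2023. If it has already taken place, the rule applied and what was disclosed should be reported instead.

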### Dissemination policy

The results of the study will be released to the public via peer-reviewed publication or academic reports.

### Statistical analysis

All data will be analyzed on the intention-to-treat population and are supplemented by per-protocol set analyses. The intention-to-treat population contains all patients who will undergo randomization (irrespective of whether they successfully receive TIPS), while per-protocol set analyses only include patients who successfully receive TIPS. Continuous variables will be summarized as mean ± standard deviation or the median values (ranges) and will be compared using the independent sample *t* test or one-way analysis of variance. Categorical variables will be expressed as frequencies and compared using the Chi-Square or Fisher’s exact tests. The missing data were performed with multiple imputation by using the MICE procedure. The time-to-event primary and secondary outcomes will be calculated by the Kaplan-Meier method and compared by the log-rank test (Mantel-Haenszel version). Data will be censored when any of the following events occur : liver transplantation, death, end of follow-up time. Estimates of treatment effect (with 95% CIs) were evaluated by using Cox regression models. Two-tailed *p* values <0.05 will be considered statistically significant. All statistical calculations will be performed using SPSS V.25.0 (Chicago, IL, USA).

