### Outcome measures

The primary endpoint of the INTIPHE trial is to compare the rate of post-TIPS overt hepatic encephalopathy between patients with left or right shunt at 24 months.

The secondary endpoints include comparing the grade and duration of hepatic encephalopathy, covert HE, the rate of shunt dysfunction, the rate of variceal rebleeding, the HE free survival, the cumulative patency rate of stent and the overall survival at 24 months between two groups.

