### Outcome definitions

The grade of HE was classified into covert HE (minimal HE and grade I) and overt HE (grade II to grade IV) according to the severity of manifestation (Table 3). Stroop Test (EncephalApp developed by Jasmohan Bajaj) will be used to detect the minimal HE. An off-time and on-time value >190 s will identify a patient with covert HE. Grade I to grade IV HE will be diagnosed by clinical examination. The starting time, duration, treatment, and outcome of every episode will be recorded.

**Table 3 Tab3:** WHC and clinical description of HE

WHC	ISHEN	Description
Minimal	Covert	Psychometric or neuropsychological alterations of tests exploring psychomotor speed/executive functions or neurophysiological alterations without clinical evidence of mental change
Grade I		Trivial lack of awareness Euphoria or anxiety Shortened attention span Impairment of addition or subtraction Altered sleep rhythm
Grade II	Overt	Lethargy or apathy Disorientation for time Obvious personality change Inappropriate behavior Dyspraxia Asterixis
Grade III		Somnolence to semi stupor Responsive to stimuli Confused Gross disorientation Bizarre behavior
Grade IV		Coma

HE-free survival (HEFS) is defined as the time from D0 to the first episode of HE.

Shunt dysfunction will be suspected in the condition of rebleeding and/or the maximum flow velocity within the shunt is less than 0.5 m/s or absent on color Doppler ultrasound (CDUS). Shunt will be further confirmed by portography if the shunt stenosis is greater than 50% and/or portal-systemic gradient (PSG) is beyond 15 mmHg, and TIPS revision by balloon angioplasty and additional stent-placement will be planned.

Variceal rebleeding is defined as bleeding from gastroesophageal varices confirmed by upper gastrointestinal endoscopy.

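### The stated tests suit HE grade and HE duration poorly: an unordered test for an ordered grade, and a test of means for a duration that is mostly zero

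*Protocol article*

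**What the plan says.** The Statistical analysis section sets tests by type of variable. Continuous variables are summarised by mean ± SD "or the median values (ranges) and will be compared using the independent sample" t test or one-way analysis of variance. For the rest, "Categorical variables will be expressed as frequencies and compared using the Chi-Square or Fisher’s exact tests". Apart from the Kaplan-Meier, log-rank and Cox methods for time-to-event outcomes, no other test is named.

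Under Outcome measures, the list of secondary endpoints opens with "comparing the grade and duration of hepatic encephalopathy". Under Outcome definitions the grade is an ordered scale: "The grade of HE was classified into covert HE (minimal HE and grade I) and overt HE (grade II to grade IV"), with the levels set out in Table 3. Duration is collected per episode: "The starting time, duration, treatment, and outcome of every episode will be recorded". On the population, the Statistical analysis section states: "All data will be analyzed on the intention-to-treat population and are supplemented by per-protocol set analyses".

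**The concern.** Two features of the stated rules fit these outcomes badly.

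- **Duration.** The plan foresees skewed variables, since it offers median and range as a summary, but still tests their means. HE duration is likely to be skewed and, in the full randomised population, zero for every patient without an episode. A few long episodes can then dominate the variance and hide a difference.
- **Grade.** Chi-square and Fisher treat none, covert, II, III and IV as unordered labels. They give the same result whichever way the categories are arranged, so a consistent shift towards milder HE earns no credit for being consistent.

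At stake is the chance of detecting a real effect on the first two secondary endpoints listed. The link from these endpoints to these tests is inferred from variable type, because the article names no test for either one. It offers no other rule under which they would fall.

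**Working it through.** The article gives no power figure for grade or duration, so there is none to reproduce. The check compares the stated tests with rank tests on the same simulated trials.

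**Inputs from the article.** 130 patients randomised 1:1, so 65 per arm. HE at two years 16.9% (left) and 33.1% (right), from Sample size calculation. Two-sided 5% level.

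**Inputs assumed, because the article does not give them.** Duration among patients with HE: log-normal, median 5 days, log-SD 0.5, 1.0 or 1.5; right/left duration ratio 1 or 1.5. Overt grades II/III/IV split 60/30/10%, or 40/40/20% on the right for a worse mix. HE-free patients score 0 or the lowest category.

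**Step 1: share of zeros.** (0.169 + 0.331)/2 = 0.25 with HE, so about 75% have zero days. Expected patients with HE: 65 × 0.169 = 11.0 left and 65 × 0.331 = 21.5 right. This reads the planning rates as overt HE, the primary endpoint. If covert episodes count, the share of zeros is lower; the article gives no covert rate.

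**Step 2: grade, all randomised patients, 65 per arm.**

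| Setting | Chi-square | Rank test | Loss (points) |
|---|---|---|---|
| None/II/III/IV, same mix in both arms | 40–41% | 57–58% | 17–18 |
| None/II/III/IV, worse mix on the right | 48–50% | 62–64% | 14–15 |
| Five classes, common odds ratio 2.43 | 51% | 74% | 23 |

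The smallest loss is 61.8 − 48.1 = 13.7 points. The five-class row assumes 45/22/20/9/4% on the right. Its odds ratio is (0.331/0.669)/(0.169/0.831) = 2.43. That row is generated under proportional odds, which favours the ordinal test. The same-mix row is not: the odds ratio is 2.43 for grade II or worse, but (0.1324/0.8676)/(0.0676/0.9324) = 2.10 for grade III or worse. The loss is there without that assumption. With 58 per arm (about 10% dropout), the same-mix comparison is 35% against 52%.

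**Step 3: duration, all randomised patients, 65 per arm.**

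| Log-SD | Duration ratio right/left | t test | Mann-Whitney |
|---|---|---|---|
| 0.5 | 1 | 48% | 58% |
| 1.0 | 1 | 28% | 56% |
| 1.5 | 1 | 15% | 58% |
| 0.5 | 1.5 | 81% | 68% |
| 1.0 | 1.5 | 53% | 63% |
| 1.5 | 1.5 | 29% | 62% |

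With equal durations the t test loses 10 to 43 points. In the low-skew row with longer right-arm episodes it gains 81 − 68 = 13.

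**Step 4: type I error, HE rate 25% in both arms.** On duration, the t test rejects in 4.3% (log-SD 1.0) and 2.9% (log-SD 1.5), and Mann-Whitney in 5.0%. On grade, chi-square rejects in 4.1–4.4% and the rank test in 5.2%. Neither stated test exceeds 5%.

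**Step 5: what the rank test on duration picks up.** When durations are equal, the arms differ only in incidence. Power of a plain two-proportion test at 65 per arm is Φ[(0.162 − 1.96 × √(2 × 0.25 × 0.75/65)) / √((0.169 × 0.831 + 0.331 × 0.669)/65)] = Φ[(0.162 − 0.1489)/0.0746] = Φ(0.176) = 57%. Mann-Whitney's 56–58% is therefore mostly the incidence difference.

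The figures in Steps 2 to 4 come from 4,000 trials per setting (6,000 for the five-class row). A repeat with 6,000 trials agreed within 2.5 points for every power in the two tables.

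**The case against.** **A reader might infer that the plan gives no valid randomised comparison of grade and duration.** The document does not support that. It places all data on the intention-to-treat population, and with HE-free patients kept, both stated tests hold their error rate (Step 4). The randomised comparison would be lost only if patients with HE were compared among themselves, about 11 against 22 selected on a post-randomisation event. The article nowhere says it will do this. In simulation with equal durations, a t test in that subset rejects in about 4% of trials. That is the test holding its level when episode durations truly do not differ, not evidence of lost power.

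**The loss for duration is not general.** Skew and effect size are assumed, and one plausible setting reverses the order. This stands.

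**The rank test on duration largely repeats the incidence comparison.** This stands for equal durations. Incidence is already the primary endpoint, and HE-free survival is analysed by time-to-event methods. A reduction in the number of patients with HE therefore has other routes to detection, and it would be too strong to say that a real benefit is likely to be missed by the trial.

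**Outcome-specific tests and scoring rules may sit in a statistical analysis plan.** They may, and their absence from an article is no fault. The point rests on what the article does state: a mean-based test for variables it expects to be skewed, and an unordered test for every categorical variable.

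**Conclusion.** The point holds as a weakness of method for two secondary endpoints. For grade, the unordered test costs roughly 14 to 23 points of power at 65 per arm in every setting tried; the size rests on assumed grade distributions, but the direction does not change across them. For duration, the t test loses about 10 to 40 points when episodes last equally long in both arms (assumed log-SD 0.5 to 1.5). It can be the stronger test when skew is low and right-arm episodes are longer. The case for changing the duration test is therefore robustness to skew, not a guaranteed gain. Validity is not in question while HE-free patients stay in the analysis. The change is worth making, but the primary analysis does not depend on it.

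**What to change.** In the Statistical analysis section, name the analysis of these two endpoints, both up to month 24 and in all randomised patients:

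- **Grade:** worst HE grade, ordered none < covert < II < III < IV, compared by a Mann-Whitney or proportional-odds test.
- **Duration:** total days in HE, 0 if none, compared by Mann-Whitney, with means kept as description.
- **HE patients only:** label any such comparison descriptive.
- **Incomplete follow-up:** state how death, transplantation and early end of follow-up enter both scores. Without a rule, a patient who dies early without HE would receive zero days and the lowest grade, the best possible result. The existing censoring rule covers time-to-event data and does not settle this.

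No new data are needed, since every episode is already recorded. The cost is a few sentences, plus a decision on the scoring of death and transplantation, which should be made before the data are seen. The downside is small: the duration test no longer corresponds to a difference in means, and with low skew it can have less power than the t test.

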### Trial assessments

The last enrolled patient will be followed up for 24 months after the start of treatment (D0). All other patients will be followed up until the final visit of the last enrolled patient. Patients will therefore be followed up for a maximum of 48 months and a minimum of 12 months following the start of treatment. All patients will be assessed by the schedule summarized in Table 2.

**Table 2 Tab2:** Trial assessment schedule

	Enrollment	Treatment			Post-TIPS follow-up					
Evaluation/examination	≤14 days before randomization	D0	D1	D2	M1	M3	M6	M12	M18	M24
Informed consent	×									
Demographics	×									
Medical History	×									
Enhanced abdominal CT	×			×		×		×		×
Ultrasound Elastography	×			×	×	×	×	×	×	×
Upper gastrointestinal endoscopy	×				×	×	×	×	×	×
Hematology^a^	×	×	×		×	×	×	×	×	×
Biochemistry^b^	×		×		×	×	×	×	×	×
Serial ammonia concentration	×		×		×	×	×	×	×	×
Tumor markers^c^	×		×		×	×	×	×	×	×
HBV-DNA	×		×		×	×	×	×	×	×
Child-Pugh	×		×		×	×	×	×	×	×
MELD^d^	×		×		×	×	×	×	×	×
ECOG^e^	×	×	×	×	×	×	×	×	×	×
HE assessment^f^	×	×	×	×	×	×	×	×	×	×
Adverse events	×	×	×	×	×	×	×	×	×	×
Survival	×	×	×	×	×	×	×	×	×	×

^a^Measurement of red blood cells, hemoglobin, white blood cells, absolute neutrophils and absolute lymphocytes,and platelets

^b^Measurement of total bilirubin, direct and indirect bilirubin, albumin, alanine aminotransferase, aspartate aminotransferase, alkaline phosphatase, glutamine transferase, urea nitrogen, serum creatinine, potassium, sodium, prothrombin time, INR, and D-dimer

^c^Measurement of AFP, CEA, and CA-199

^d^Model for End-stage Liver Disease scores

^e^Eastern Cooperative Oncology Group

^f^Measured by Stroop Test and clinical examination

Additional non-study assessments are permitted at the discretion of the treating investigator. Follow-up will be discontinued if the patient receives liver transplantation, if the patient withdraws consent, or if a physician considers it necessary for the patient to discontinue the trial from a medical perspective.

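### Kaplan-Meier with death and transplantation censored will overstate the 24-month overt HE rate; the log-rank test and Cox model are not invalidated

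*Protocol article*

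**What the plan says.** Under Outcome measures, the primary endpoint is to "compare the rate of post-TIPS overt hepatic encephalopathy between patients with left or right shunt at 24 months". It is therefore a probability of overt HE by a fixed time.

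Under Statistical analysis, the method is: "The time-to-event primary and secondary outcomes will be calculated by the Kaplan-Meier method and compared by the log-rank test (Mantel-Haenszel version". The censoring rule follows: "Data will be censored when any of the following events occur : liver transplantation, death, end of follow-up time". Death and transplantation thus have the same status as reaching the end of follow-up. Effects come from Cox models: "Estimates of treatment effect (with 95% CIs) were evaluated by using Cox regression models".

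Three other places bear on the point:

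- Trial assessments: "Follow-up will be discontinued if the patient receives liver transplantation, if the patient withdraws consent". No HE after transplantation would be recorded.
- Outcome definitions: "HE-free survival (HEFS) is defined as the time from D0 to the first episode of HE". Death is not an event in this endpoint despite its name.
- Statistical analysis: "Categorical variables will be expressed as frequencies and compared using the Chi-Square or Fisher’s exact tests". This is a general sentence that does not mention the primary endpoint.

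The article names no cumulative incidence function, no competing-risk method and no composite of HE with death.

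**The concern.** Censoring a patient in a Kaplan-Meier analysis treats that patient as still able to have the event, at the same rate as those still observed. This suits a patient who has reached the end of follow-up. It does not suit a patient who has died. With deaths and transplantations censored, one minus Kaplan-Meier describes a hypothetical population in which neither occurs, and only if those events are unrelated to HE risk. That is doubtful here: the article itself calls the Child-Pugh score an independent prognostic factor for post-TIPS HE (Study limitations), and a score of liver severity plausibly also predicts death and transplantation.

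At stake are the two HE percentages and their difference, which readers will take as the trial's result. The Discussion says that a reduction with the left branch might lead to its recommendation as the standard procedure for patients at high risk of HE. The absolute rates should therefore be those that patients actually experience.

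The same censoring rule governs the time-to-event secondary outcomes, so variceal rebleeding and shunt dysfunction share the problem if they are analysed that way.

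**Working it through.** **Inputs from the article.** Sample size calculation: "We presume that the rate of HE after 2 years of TIPS shunting left and right branches will be 16.9% and 33.1%, respectively". The planned difference is 33.1 − 16.9 = 16.2 points. These rates are for HE, not expressly overt HE, and serve here only as illustrative one-minus-Kaplan-Meier values.

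**Assumed input.** The article gives no 24-month probability of death or transplantation. Let q be the *net* competing risk, meaning the risk by 24 months if HE did not occur. I take q = 5%, 10%, 20% and 30%.

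**Direction.** One minus Kaplan-Meier, with competing events censored, is never below the cumulative incidence. It is strictly above it once any HE event follows a competing event. This needs no assumption about q.

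**Size, under constant cause-specific hazards.** For a one-minus-Kaplan-Meier value p:

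- cumulative HE hazard A = −ln(1 − p): 0.1851 (left), 0.4020 (right)
- cumulative competing hazard B = −ln(1 − q): 0.0513, 0.1054, 0.2231, 0.3567 for the four values of q
- cumulative incidence of HE = A/(A + B) × [1 − (1 − p)(1 − q)]

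Example, right branch, q = 10%: 0.4020/0.5074 × (1 − 0.669 × 0.90) = 0.7923 × 0.3979 = 0.315.

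| Net competing risk q | Left: 16.9% becomes | Right: 33.1% becomes | Overstatement, left / right (points) | Difference: 16.2 becomes |
|---|---|---|---|---|
| 5% | 16.5% | 32.3% | 0.4 / 0.8 | 15.8 |
| 10% | 16.1% | 31.5% | 0.8 / 1.6 | 15.5 |
| 20% | 15.2% | 29.9% | 1.7 / 3.2 | 14.7 |
| 30% | 14.3% | 28.2% | 2.6 / 4.9 | 13.9 |

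Differences are taken before rounding.

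**What q means.** It is not the share of patients who would be seen to die or be transplanted before HE. That share is B/(A + B) × [1 − (1 − p)(1 − q)]. For q = 10% it is 9.1% (left) and 8.3% (right); for q = 30% it is 27.5% and 25.0%.

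**Unequal competing risks.** With q = 10% left and 30% right, the incidences are 16.1% and 28.2%, a difference of 12.1 points. With 30% left and 10% right they are 14.3% and 31.5%, a difference of 17.2 points. Kaplan-Meier gives 16.2 both times, so the bias in the difference can go either way.

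**Scale against sampling error.** At 65 per arm and the planning rates, the 95% half-width for a simple difference in proportions is 1.96 × √[(0.169 × 0.831 + 0.331 × 0.669)/65] = 0.146, or 14.6 points. At equal competing risks the bias in the difference is 0.4 to 2.3 points.

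**The case against.** The strongest reply is that the trial's inference does not depend on this estimator. Significance comes from the log-rank test and the effect estimate from Cox regression. With competing events censored, both validly compare the cause-specific hazard of HE, and that quantity suits the partly mechanistic question of whether laminar portal flow makes the branch matter. This stands. A reader might infer that the primary test is invalid; the documents do not support that.

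A second reply is that the rate might be reported as a crude proportion with a Chi-square or Fisher test, where this overstatement would not arise. That is possible, but the sentence on those tests concerns categorical variables in general, while the Kaplan-Meier sentence names primary outcomes expressly.

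A third is that the effect is small. Eligibility is limited to Child-Pugh A or B and excludes bilirubin above 51 μmol/L and illness that may reduce life expectancy. The Introduction's median survival of under 2 years is background on advanced cirrhosis. A reader might take it as this trial's expected mortality, but nothing in the article supports that. The small size relative to sampling error also stands; it limits the severity but does not remove a systematic error that is cheap to avoid.

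Three further overreadings should be avoided:

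- That HE is impossible after transplantation. The article shows only that follow-up ends there.
- That death or transplantation differs by branch. No passage suggests it, and the unequal-risk figures are illustrations.
- That censoring death is wrong for stent patency. It can be a deliberate measure of device performance.

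**Conclusion.** The point holds for the estimated rate, not for the test. The article fixes both the Kaplan-Meier method and the censoring of death and transplantation, for an endpoint defined as a 24-month rate, and no other passage repairs the mismatch.

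The upward direction in each arm is certain once HE events follow competing events. The size is conditional on an assumed net competing risk of 5–30%, constant hazards and the planning rates: 0.4 to 2.6 points on the left and 0.8 to 4.9 points on the right. If HE tended to occur before most deaths and transplantations, the overstatement would be smaller than this. The effect is modest beside the trial's sampling error, but it bears on the primary endpoint as defined and should be corrected in the analysis plan.

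**What to change.** - Estimate the 24-month overt HE rate in each arm, and the between-arm difference with its 95% CI, by the Aalen-Johansen cumulative incidence function, with death and liver transplantation as competing events.
- Keep the log-rank test as the primary test and Cox as the effect estimate, and label both as comparisons of the cause-specific hazard of HE.
- Use the same cumulative incidence estimate for variceal rebleeding and shunt dysfunction. Stent patency may stay as a Kaplan-Meier estimate with death censored if it is labelled a device-performance measure.

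The cost is a few sentences in the analysis plan and a short script outside SPSS, for example in R. No extra patients or visits are needed: survival is already assessed at every visit, and transplantation already ends follow-up, so only the dates of these events are required. Reported HE rates will be slightly lower than under the current plan.
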